#### 2.11.2. Randomization

Randomization will be performed by a researcher not involved with recruiting and assessing the participants and will be generated via Microsoft Excel software 2019, before the beginning of the main study. Randomization will be stratified according to gender and the frequency of LBP. Treatment allocation will be concealed through sealed, opaque envelopes sequentially numbered. After the baseline assessment, one of the researchers responsible for the intervention will open the sealed envelopes to identify the group to which the participant was allocated: (1) with active breaks (AB-group); (2) with self-care recommendations (C-group).

#### 2.11.3. Blinding

The evaluation team will consist of four collaborators, one of whom will provide the interventions, one will evaluate the outcomes, one will randomize the participants and the last one will complete the statistical analysis. Double blinding will be used, with participant- and assessor-blinded. The participants will be blinded throughout the trial. All participants will be instructed that they will be allocated to one of the two protocols without knowing to which protocol. All the pre- and post-treatment assessments will be performed by a assessor blinded to the group allocation and treatment. The statistician performing the statistical analyses will also be blinded to the group allocation and treatment.

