### 2.8. Active Break Program

The experimental group will receive recommendations to take an active break every 30 min of sitting for 12 weeks. In the experimental intervention, the active break program will include lumbar and hip extension exercises and will be based on self-education with an explanation of the importance of regular training. The participants will receive a booklet with photographed and described exercises. The education will be carried out by an experienced physiotherapist.

The habit of doing exercises during an active break will be formed gradually (Table 2). In the first month, participants will be instructed to perform the proposed exercises in a standing position with lumbar and hip extension every 30 mins or whenever musculoskeletal discomfort occurs. In the second month, the complexity of the active break exercises will be increased by progressing to spine hyperextension exercise. In the third month, participants will be instructed to also perform spine hyperextension exercise in a sitting position. The number of repetitions depends on the needs of the participants.

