### 2.9. Control Group

Participants assigned to the control group will receive an educational self-care book containing information on LBP, the anatomy of the spine and its relationship to the muscular chain, care during daily life activities and the importance of regular physical exercises. The control group will perform their regular baseline activities and will be advised to not alter their current behavior routine. Participants will be asked not to look for other treatments outside the trial during the intervention period.

Participants assigned to the control group will be offered the option of joining the exercise program with an active break after the final assessment has been completed.

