### 2.10. Procedure

All 1st- and 2nd-year students of Physical Education will be informed of the research procedures, and those that are interested will be provided with a brief introduction to the selection process. One researcher from the university will conduct a pre-screening self-administered questionnaire (on paper) during classes with students. The pre-screening will address basic demographic data, the frequency of LBP, and the specific inclusion and exclusion criteria for this study. LBP will be assessed using the following question: “Have you experienced low back pain for the last 3 months?”. The answer options were: “no”, and “yes”. “Yes” was considered to denote the presence of LBP. A blinded assessor will evaluate the eligibility criteria. Participants who meet the inclusion criteria will be invited to the main study.

Before the baseline assessment, written consent will be obtained from the participants. At the baseline assessment session, participants will be requested to complete the VAS, Revised ODI, and Borg-10 scale. The baseline assessment will be conducted before the random distribution of the participants into the groups. After completion of the baseline assessment, participants will be randomly assigned into one of the two groups (AB-group or C-group), and simultaneous implementation of the two programs will commence. To improve adherence, participants from AB-group will send daily reports about hours in sitting positions and the number of active breaks via the Messenger^®^ application. Participants from C-group will be asked not to look for other treatments outside the trial during the interventions.

The assessment of the outcomes will be collected at baseline and immediately after the 12-week intervention.

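### Section 2.11.3 claims double blinding with participants blinded throughout, but the two programmes are openly different and every outcome is self-rated, so the ratings are not protected from expectation bias

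*Protocol article*

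**What the plan says.** Section 2.11.3 makes the claim in two sentences: "Double blinding will be used, with participant- and assessor-blinded. The participants will be blinded throughout the trial". The only means it gives for participants is this: "All participants will be instructed that they will be allocated to one of the two protocols without knowing to which protocol". It adds that the outcome assessor and the statistician are blinded.

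The arms are described elsewhere:

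- **Active break arm (2.8, 2.10).** "The experimental group will receive recommendations to take an active break every 30 min of sitting for 12 weeks". A physiotherapist teaches the programme. Of the materials, 2.8 says: "The participants will receive a booklet with photographed and described exercises". Section 2.10 adds that "participants from AB-group will send daily reports about hours in sitting positions and the number of active breaks".
- **Control arm (2.7, 2.9).** Participants get a self-care book, are encouraged to stay active, and "will be advised to not alter their current behavior routine". They "will be offered the option of joining the exercise program with an active break after the final assessment has been completed".

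Sections 2.4 to 2.6 list five primary outcomes (frequency of low back pain, VAS, ODI, Borg discomfort and GPE) and one secondary outcome, a self-completed questionnaire.

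**The concern.** Not knowing the allocation in advance is different from not knowing it for 12 weeks. The mechanism in 2.11.3 can hold until the envelope is opened. It cannot outlast the start of a programme that the participant has to learn, carry out and count.

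This matters because the outcomes are self-ratings. If the trial is reported as double-blind, readers will take differences in pain, disability, discomfort and perceived effect as protected from expectation and reporting bias. GPE is the most exposed. It asks about change since treatment began, has no baseline value, and is put to one group that has followed a new programme and another that was advised to keep its routine.

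**Working it through.** The claim involves no figure from the plan, so the check compares sections.

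**Step 1. Can a participant tell which programme they are in?**

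| Feature | Active break arm | Control arm | Section |
|---|---|---|---|
| Material | Exercise booklet | Self-care book | 2.8, 2.9 |
| Teaching | Physiotherapist explains the exercises | None described | 2.8, 2.9 |
| Behaviour asked for | Break for each 30 min of sitting, 12 weeks | Usual activities, no change of routine | 2.8, 2.9 |
| Daily reporting | Sitting hours and number of breaks | None described | 2.10 |
| Sham or look-alike programme | None described | None described | 2.7 to 2.9 |

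Section 3 adds exercise logs, and praise for adhering and returning them. A participant who performs and counts active breaks knows it, and so does one who was asked to change nothing. Participants are also students of one Bachelor's course (2.1), so comparing notes is easy.

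**Step 2. Who makes the outcome rating?**

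| Outcome | Rated by | Section |
|---|---|---|
| LBP frequency | Participant, by questionnaire | 2.4 |
| VAS | Participant, by marking a line | 2.5.1 |
| ODI | Participant, by completing the form | 2.5.2, 2.10 |
| Borg CR-10 | Participant, by body region | 2.5.3 |
| GPE | Participant, on a 7-point scale | 2.5.4 |
| Post-Intervention Questionnaire | Participant, self-completed | 2.4, 2.6 |

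All six are participant ratings. The blinded assessor runs the session and collects the answers but does not form the judgement.

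**Step 3. What do the other safeguards cover?** Concealed, numbered envelopes (2.11.2) protect the assignment step. A blinded statistician (2.11.3) protects analytic choices. A blinded assessor can limit unequal handling or prompting, for example during the one-hour sitting test. None of them changes what a participant who knows their programme writes down.

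**Step 4. Does the article acknowledge this elsewhere?** The limitations in section 4 mention dropout and bias in monitoring the frequency and quality of breaks. They do not mention unblinded self-report.

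**Illustration only.** The documents give no size for a reporting shift. Assume a true effect of zero and a shift of b standard deviations in one arm, tested by a two-sided two-sample t-test at 0.05. The noncentrality is b × √(n/2), with 2n − 2 degrees of freedom. At n = 32 per arm (2.11.1) this is 4b. At n = 25 per arm (half of the required 50) it is 3.54b.

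| Assumed b (SD) | False-positive rate, n = 32 | False-positive rate, n = 25 |
|---|---|---|
| 0 | 5.0% | 5.0% |
| 0.1 | 6.8% | 6.4% |
| 0.2 | 12.4% | 10.7% |
| 0.3 | 21.9% | 18.0% |
| 0.5 | 50.4% | 41.0% |

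The table shows only the direction and how quickly the error rate would grow. The finding does not depend on it.

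**The case against.** The strongest reply is that blinded here means unaware of which protocol is the experimental one. Both arms get printed material and a named protocol, and controls receive real content on back care and regular exercise. The sentence on allocation could be read this way. But the article does not say so, and an arm with a new programme and daily reports set against one advised not to change makes it doubtful. Even if true, it would be blinding to the hypothesis, and double blinding would still be the wrong label. What stands is that the authors should state what participants are told.

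It is also fair to say that participant blinding is rarely achievable for an overt exercise programme. That is why the remedy concerns the description and not the design.

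Three stronger readings are tempting, and the documents do not support them:

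- **That the trial has no protection from bias.** Concealed allocation and the blinded assessor and statistician are real. What is missing is participant blinding of self-ratings.
- **That controls are unblinded by the later offer of the programme.** Section 2.9 places that offer after the final assessment and does not say that controls hear of it sooner.
- **That every student learns the content of both arms beforehand.** Section 2.10 says only that students are informed about the research procedures. It does not say that arm content or the hypothesis is disclosed.

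The conclusion needs none of these. The difference between the programmes is enough.

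**Conclusion.** The statement in 2.11.3 is wrong as written. Participants will know which programme they follow, and since they rate all five primary outcomes and the secondary questionnaire, assessor blinding does not shield those ratings from expectation or reporting bias. This is an affirmative statement contradicted by the article's own sections, so condensation of a fuller protocol does not explain it.

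The size of the bias cannot be derived from the document. A reader might infer that a given share of the planned effect of d = 0.50 would be expectation, or that the results will be invalid. Neither follows: the document gives no reporting shift, and the direction and extent of any bias are unknown. The conclusion rests on two readings of the text: that no sham is used, since none is described, and that the outcomes are collected as sections 2.4 to 2.6 and 2.10 set out.

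**What to change.** 1. In 2.11.3, remove the double-blinding label and the claim that participants stay blinded. State instead that participants and the intervention provider are not blinded, and that the assessment staff and the statistician are.
2. In the same section, say what participants are told about the two protocols and about the study hypothesis. If they are kept unaware of which protocol is experimental, describe that as such and say how.
3. In the limitations (section 4) and in the conclusions, state that all primary outcomes are unblinded self-reports and that between-group differences may include expectation effects.

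The cost is rewording and a less favourable blinding description. Arms, outcomes, sample size and analysis stay as they are. Adjusting for participants' expectations measured after allocation is not a substitute: such a measure can itself be influenced by the arm, so adjustment cannot be relied on to remove the bias.

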## 3. Study Participants Protocol Adherence

Participants are encouraged to adhere to the intervention. The intervention is determined based on the number of active breaks and adherence to recommendations. Commitment to the treatment group will be checked using an exercise log, text messaging and meetings. Every second day, the study coordinator will text participants and enquire about their protocol adherence or adverse events. Participants will also be encouraged to contact the study coordinator in case of any problems. Participants will receive positive feedback and reinforcement if they adhere to their intervention and return their exercise logs.

### 3.1. Statistical Analysis

The data will be analyzed using Statistica 14.0.0.15 program (TIBCO Software Inc., Palo Alto, CA, USA, 2020). The parameters will be described using basic descriptive statistical measurements, i.e., the percentage for qualitative variables, and the mean and standard deviation for quantitative variables. For variables that do not meet the criteria of normality of distribution, data will be presented as medians and quartile ranges. The normality of the distributions of the quantitative variables under study will be tested using the Shapiro–Wilk test. To verify the homogeneity of variances, Lavene’s test will be conducted. The chi-square test will be used for categorical variables. Descriptive statistics will be calculated separately for all groups (active break vs. control). The Student’s *t*-test (if data meet the criteria of normality of distribution) and the Mann–Whitney U test (if data do not meet the criteria of normality of distribution) will be used to compare parameter values between groups (active break vs. control). The Wilcoxon signed rank test will be used to examine the differences in parameters (VAS, ODI and discomfort) before and after the intervention. Intention-to-treat analysis will include all randomized patients. The significance level will be set at *p* < 0.05.

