### 2.3. Pre-Intervention Questionnaire

The survey contained questions regarding:-gender,-age,-current physical activity (sports discipline, number of training days and hours per week),-illnesses, injuries, surgical history due to spinal problems, treatment related to LBP, diagnosed defects in body posture,-experience of LBP within the last three months. Individuals who respond positively (“yes”) to the question “Have you experienced low back pain for the last three months?” will then answer the question in the frequency of experiencing LBP (rarely, few times per week, often, or constantly) and the types of situations in which LBP occurred or increased.

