### 2.4. Outcome Measures

The primary outcomes will be the frequency of LBP (questionnaire), pain intensity (VAS), disability index (ODI) and perceived musculoskeletal discomfort during prolonged sitting (Borg scale), assessed at baseline and after the 12-week intervention, and the Global Perceived Effect (7-point Likert scale), assessed only after the 12-week intervention. The secondary outcome will be the Post-Intervention Questionnaire (5-item self-completed questionnaire), assessed only after the 12-week intervention. Table 1 shows the distribution of the different measures across the time points during the present study.

All the tests will be performed during morning hours in the laboratory room at the Regional Centre for Research and Development in Biala Podlaska.

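### LBP frequency, an ordered primary outcome, falls by elimination to a chi-square test that ignores the ordering and costs roughly 15 to 25 points of power against a rank test

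*Protocol article*

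**What the plan says.** All references are to the protocol article.

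- **Outcome status.** Section 2.4 states: "The primary outcomes will be the frequency of LBP (questionnaire), pain intensity (VAS), disability index (ODI", followed by discomfort and the Global Perceived Effect. LBP frequency is to be measured at baseline and after the 12-week intervention.
- **Scale.** Section 2.3 asks participants who report LBP in the last three months for "the frequency of experiencing LBP (rarely, few times per week, often, or constantly"). These are four levels with a natural order.
- **Tests.** Section 3.1 states: "The chi-square test will be used for categorical variables". The t-test or its alternative, "the Mann–Whitney U test (if data do not meet the criteria of normality of distribution"), depends on a normality check that the section applies to quantitative variables. The before-after test is limited to three other measures: "The Wilcoxon signed rank test will be used to examine the differences in parameters (VAS, ODI and discomfort) before and after the intervention".
- **Baseline use.** Section 2.11.2 states: "Randomization will be stratified according to gender and the frequency of LBP".

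No test is assigned to LBP frequency by name, and no trend, ordinal or exact test appears. The abstract, section 2.5 and Table 1 do not list LBP frequency among the outcomes, so its status also needs to be reconciled.

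**The concern.** A shift towards less frequent pain is the effect that active breaks are meant to produce on this scale. Pearson chi-square gives the same answer whichever way the four levels are arranged, so it cannot use the fact that a shift runs in one direction. It also leaves out baseline frequency, which is collected and used as a stratification factor. At stake is the chance of detecting a real effect on a primary outcome in a trial of only 64 people.

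**Working it through.** **Inputs from the documents.** Four ordered levels (2.3); alpha 0.05 (3.1, taken as two-sided because the sidedness is not stated); 50 participants required, raised to 32 per arm, and planned power 0.85 (2.11.1). The dropout step reproduces: 25 / (1 − 0.20) = 31.25, rounded up to 32. The plan states no power for LBP frequency, so there is no plan figure to reproduce for this outcome.

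**Inputs that are assumptions.** The control distribution of LBP frequency and the treatment effect. The effect is modelled as one common odds ratio (OR) across all cut-points. Example with control 40/35/18/7% and OR 3:

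- cumulative control shares 0.40, 0.75, 0.93 have odds 0.667, 3, 13.29
- multiplied by 3: 2, 9, 39.86
- back to shares: 0.667, 0.900, 0.976
- active-break (AB) arm: about 67/23/8/2%

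**Step 1, cost of the extra degrees of freedom.** For a pure ordered shift, a 1-df test with 85% power has noncentrality 8.98. The same noncentrality gives 71% power on 3 df and 66% on 4 df.

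**Step 2, simulation.** Pearson chi-square against tie-corrected Mann–Whitney, 32 per arm, 40,000 trials per setting, power in %:

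| Assumed control distribution | OR 2.5 | OR 3 | OR 4 |
|---|---|---|---|
| 25/25/25/25 | 36 v 52 | 49 v 66 | 70 v 85 |
| 40/35/18/7 | 31 v 48 | 43 v 61 | 62 v 80 |
| 55/25/15/5 | 26 v 42 | 35 v 53 | 51 v 71 |
| 10/40/30/15/5 (first level no LBP) | 27 v 50 | 39 v 64 | 61 v 83 |

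The loss is about 15 to 20 points with four levels and 22 to 25 with five. A further five-level setting (15/35/30/15/5%, OR 3) gave about 0.42 against 0.65 at 32 per arm, and about 0.31 against 0.55 at 25 per arm.

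**Step 3, the loss in participants.** With 40/35/18/7%, 85% power needs 78 against 57 per arm at OR 3, and 52 against 38 at OR 4. 78/57 = 1.37 and 52/38 = 1.37, so chi-square needs about 37% more participants.

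**Step 4, validity.** With no effect, chi-square rejected in 3.8 to 5.1% of trials across the settings at 25, 29 and 32 per arm.

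**Step 5, sparse cells.** With equal arms of 32, an expected count is 32 × the pooled share of that level. It is below 5 when the share is below 5/32 = 15.6%. In a 2×4 table one such level puts 2 of 8 cells (25%) below 5.

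- 40/35/18/7% at OR 3: pooled shares are about 53/29/13/5%, so expected counts are about 17, 9, 4 and 1.5.
- Even control distribution at OR 3: pooled shares are 37.5/25/20/17.5%, so expected counts are 12, 8, 6.4 and 5.6.

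In simulation, more than 20% of cells fell below 5 in 93 to 99% of trials for the skewed distributions in the table. For the even distribution this was 10% (no effect) to 57% (OR 4).

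**Step 6, participants who answer no.** This matters only if the week-12 form reuses the gate in section 2.3. With OR 3 and 32 per arm:

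- 3% no LBP in controls: 32 × 0.03 ≈ 1. In the AB arm the odds are 3 × 0.03/0.97 = 0.093, a share of 0.085, so about 3 people.
- 15% in controls: 32 × 0.15 ≈ 5. In the AB arm the odds are 3 × 0.15/0.85 = 0.529, a share of 0.346, so about 11 people.

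If these participants had no level and were dropped, chi-square power would go from 0.37 to 0.35 in the first case and from about 0.42 to 0.17 in the second.

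**The case against.** **Chi-square is never assigned to this outcome by name.** Gender and the dichotomised Global Perceived Effect fit the chi-square sentence directly, and the Mann–Whitney sentence speaks loosely of parameter values, which might cover LBP frequency. This stands as a caution: the assignment is by elimination. But the looser reading leaves two candidate tests for a primary outcome, and the same sentence of repair settles it.

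**Its primary status is unclear.** The abstract, section 2.5 and Table 1 omit it. True, but section 2.4 is the section that defines the outcomes, and it includes it.

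**A reader might infer that chi-square is unreliable here because the table is sparse.** The documents do not support this. Type I error holds, and sparsity is likely only if the upper levels are rare, which the plan does not tell us. Most of the power loss comes from the extra degrees of freedom.

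**A reader might also infer that everyone pain-free at week 12 will be excluded, biasing the result towards no effect.** This goes too far. The gate is described only for the pre-intervention questionnaire, and the wording of the week-12 item is not given. If the question were reused, its three-month recall would span almost the whole intervention, so a participant with pain early on would still answer yes. Section 3.2 attributes missing data to discontinuation and unexpected events, and a no is an answer. What remains is a conditional risk that scoring can remove.

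**Model detail belongs in an analysis plan.** Coding and covariates may well be left there. The choice of test for this class of variable is different, because section 3.1 already makes it.

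**Conclusion.** The point holds as one of efficiency. By elimination, the plan gives an ordered primary outcome a valid test that ignores the ordering. Under the assumed distributions, at 32 per arm and odds ratios of 2.5 to 4, the loss is roughly 15 to 25 percentage points of power, or about 37% more participants for 85% power in the one distribution where this was worked out. These figures assume a consistent shift across the levels, which is the pattern that favours a rank test. The number of participants affected by a possible gate at week 12 is also an assumption: from about 1 control and 3 AB to about 5 and 11 at odds ratio 3. Neither invalidity of chi-square nor a certain loss of pain-free participants follows from the documents.

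**What to change.** In section 3.1:

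1. State that week-12 LBP frequency is compared between arms with an order-using test. At minimum this is the tie-corrected Mann–Whitney U test already named. A proportional-odds model with arm, baseline frequency and gender is an alternative if the data support it.
2. Keep chi-square for nominal or binary variables.
3. If the week-12 form uses the yes/no gate, score a no as the lowest level (no LBP < rarely < few times per week < often < constantly), so that these participants are not treated as missing under section 3.2.

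Also bring the abstract, section 2.5 and Table 1 into line with section 2.4 on whether LBP frequency is a primary outcome.

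The cost is a few sentences. No extra data are needed beyond the frequency item that section 2.4 already plans, provided the week-12 form records a no. The result would rest on a rank or proportional-odds summary in place of a plain table test, and the covariate model may be unstable with rare levels in 50 to 64 people. For that reason the rank test is the safe minimum.

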### 2.11. Study Procedures

#### 2.11.1. Sample Size

The sample size was determined using the software G*Power 3.1, which used Factorial ANOVA with assumption of a medium-sized effect (d = 0.50) at a significance level of 0.05 and statistical power of 0.85. Therefore, the required sample size for this study will be 50 participants randomly assigned in two different groups. The sample will be increased by 20% to compensate for possible dropouts, leading to 32 individuals in each group (overall sample = 64 participants).

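### A Shapiro–Wilk test on the trial data chooses between a mean test and a rank test for VAS, ODI and Borg, so the hypothesis behind each primary result is not fixed in advance

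*Protocol article*

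**What the plan says.** All of this is in the protocol article, section 3.1 (Statistical Analysis), unless another section is named.

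- Normality: "The normality of the distributions of the quantitative variables under study will be tested using the Shapiro–Wilk test". No threshold is given, nor whether the test is run per arm or on pooled data.
- Between-arm test: Student's t is used "if data meet the criteria of normality of distribution) and the Mann–Whitney U test" takes over otherwise, that is, "if data do not meet the criteria of normality of distribution) will be used to compare parameter values between groups".
- Variances: "To verify the homogeneity of variances, Lavene’s test will be conducted". Nothing is said to follow from the result, and no unequal-variance test is named. Normality is the only condition attached to Student's t.
- Summaries: the same normality criterion moves the description from mean and SD to median and quartiles.
- Before–after change: the Wilcoxon signed rank test is named outright, with no gate.
- Alpha: "The significance level will be set at *p* < 0.05".

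Section 2.4 lists VAS, ODI and Borg discomfort among the primary outcomes; these are the quantitative scales that the rule governs. Section 2.11.1 sizes the trial with "Factorial ANOVA with assumption of a medium-sized effect (d = 0.50) at a significance level of 0.05 and statistical power of 0.85", an effect on the scale of means, and plans 32 per arm.

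**The concern.** The rule is stated text, not a detail left to another document. Student's t asks whether the means differ. Mann–Whitney asks whether scores in one arm tend to rank above those in the other. These are different hypotheses with different effect measures, and the two can disagree. Under section 3.1 the choice for each primary scale is made by a significance test on a small sample after the outcomes are in. A reader of the protocol cannot tell whether the VAS result will be a mean difference or a statement about ranks.

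This matters most if the active breaks help some students and not others. The spread or shape of the scores then changes, Mann–Whitney can be significant with no difference in means, and the result can be taken for a mean reduction in pain. Separately, a t-test that assumes equal variances is exposed if completers and SDs both differ between arms.

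**Working it through.** **Inputs.** From the documents: 32 per arm; alpha 0.05; the test rule; complete-case analysis with under 10% missing expected (section 3.2); a 20% dropout allowance (section 2.11.1). Assumed, because the documents do not give them: score distributions and SDs, two-sided testing, and Shapiro–Wilk at 0.05 in each arm with Student's t only if both arms pass.

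**The plan's own figure.** The plan states no error rate for the rule beyond alpha. The arm size reproduces from its base: 25/(1 − 0.20) = 31.25, rounded up to 32 per arm, 64 in all. Whether the base of 50 follows from the stated effect size is a separate matter and is not used here.

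**Step 1: which test is chosen.** Simulated at 32 per arm:

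- Exactly normal scores: both arms pass in about 90% of trials (0.95² = 0.9025), so about one trial in ten goes to Mann–Whitney by chance.
- VAS with mean 3 and SD 2: 77% pass if recorded to 0.1 cm, 32% if rounded to whole centimetres.
- ODI-like gamma score (shape 2, mean 12): about 3% pass.
- Borg-like score with 25% zeros: under 1% pass.

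The choice therefore depends on sampling chance and even on recording precision.

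**Step 2: error when both arms share a distribution.** The two-step rule rejects in 4.4–5.5% of trials across the shapes tried. Overall alpha is not inflated. Conditional on the branch taken it drifts: with normal data, Mann–Whitney after a failed pre-test rejects in 6.3–7.0%.

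**Step 3: equal means, different shape.** One arm gamma (shape 1.5, mean 3), the other normal (mean 3, SD 1.5), 4,000 trials per case. The rule is significant in 11% at 26 per arm and 14% at 32 per arm; a repeat run gave 12–15%. Welch's t gives 5–6%. Other assumed shapes (exponential or gamma scores with equal means and unequal spread or shape, 25–32 per arm) give 16–24% for the rule and 5.3–6.1% for Welch. For gamma shape 1 v 4 the figure rises with sample size (19% at 25 per arm, 24% at 32), as expected of a test with power against a different hypothesis.

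**Step 4: Student's t with unequal variances.** The true variance of the mean difference is V = s1²/n1 + s2²/n2. Student's t estimates on average P = [((n1−1)s1² + (n2−1)s2²)/(n1+n2−2)] × (1/n1 + 1/n2). Its real error is approximately Pr(|t_ν| > c√(P/V)), where c is the nominal critical value on n1+n2−2 degrees of freedom and ν the Welch degrees of freedom.

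| n1 (SD) v n2 (SD) | V | P | c√(P/V) | ν | Approx. error | Simulated Student | Simulated Welch |
|---|---|---|---|---|---|---|---|
| 32 (2) v 32 (1) | 0.156 | 0.156 | 1.999 | 45.6 | 5.2% | 4.7–5.0% | 4.5% |
| 26 (1.5) v 32 (1) | 0.118 | 0.109 | 1.924 | 41.9 | 6.1% | 6.2% | 5.1% |
| 25 (2) v 32 (1) | 0.191 | 0.165 | 1.859 | 33.3 | 7.2% | 7.0% | 4.9% |
| 22 (2) v 32 (1) | 0.213 | 0.170 | 1.790 | 28.3 | 8.4% | 8.1–8.4% | 5.0–5.1% |
| 22 (1) v 32 (2) | 0.170 | 0.214 | 2.248 | 48.2 | 2.9% | 2.8% | 4.7% |

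With equal arms P = V, so the error stays close to 5%. The error is too high when the smaller arm has the larger SD and too low when the larger arm has it.

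**Step 5: how unequal can the arms become?** 10% of 64 is 6.4, so section 3.2 implies at most 6 missing. If all six fall in one arm, the split is 26 v 32. The 25 v 32 and 22 v 32 cases need 7 and 10 losses. That exceeds section 3.2 but lies within 20% of 64 = 12.8 (section 2.11.1).

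**Step 6: cost of a fixed Welch test.** For normal data with equal variances, d = 0.50 and 32 per arm, simulated power is 50% for both Student's t and Welch.

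**The case against.** The strongest reply is that the rule is written in advance and applied by a statistician blinded to allocation (section 2.11.3), so it leaves little room for choosing the favourable test, and that it keeps overall alpha near 5%. Both statements are right. They answer a charge of manipulation or general inflation; they do not fix what is being tested.

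Three stronger readings are tempting, and the documents do not support them.

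- *Student's t will be kept whatever Levene's test shows.* A reader might infer this because normality is the only condition given. Section 3.1 says only that the test is run, and is silent on what follows. The accurate statement is that no consequence is stated.
- *The error rates are wrong.* Not for the planned design: Student's t holds at 32 per arm even with a 2:1 SD ratio. The excess needs unequal analysed arms and unequal SDs together, with the larger SD in the smaller arm. In the opposite direction the test is conservative. The larger figures need more loss than section 3.2 expects.
- *Testing VAS, ODI and Borg under different hypotheses is itself a fault.* It is not. A plan may name a mean comparison for one scale and a rank method for another. The fault is that the data make the choice.

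It also stands that the 11–15% is no false-positive rate for Mann–Whitney as such, since the two distributions do differ. It is an error only if the result is reported as a difference in means, and section 3.1 does plan medians for non-normal data.

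**Conclusion.** The point holds in a limited form. For each quantitative primary scale, the hypothesis and the effect measure are set by a normality pre-test on the trial data. The main harm is an unfixed estimand: in the equal-means case the rule is significant in about 11–15% of trials against 5–6% for Welch (higher under some other shapes), which misleads if read as a mean difference. The secondary harm is modest: about 6% for Student's t at 26 v 32 with SD ratio 1.5, the largest imbalance consistent with section 3.2, and about 8% at 22 v 32 with ratio 2.

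These sizes rest on assumed shapes and SDs and on Shapiro–Wilk applied per arm at 0.05; the documents give none of these, so they are ranges and not predictions. The finding about the rule itself needs no assumption. It is a change that should be made, not a fatal flaw.

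**What to change.** In section 3.1, name one between-arm analysis per quantitative primary scale, to be used whatever the pre-tests show. For example:

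- VAS and ODI: difference in means with Welch or heteroscedasticity-robust standard errors and a 95% confidence interval.
- Borg: one named rank or ordinal method, with its effect measure.
- The alternative test for each scale: reported as a sensitivity analysis only.

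Remove Shapiro–Wilk and Levene's test as gates; they can stay as description. Wherever a t-test is used, make it Welch's.

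The cost is a few sentences and no new data. Welch loses no appreciable power when variances are equal. The one downside is that a fixed mean-based test may lose some power to a rank test on a very skewed scale, possibly ODI here; the sensitivity analysis would show this.
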